**Figure 1 Fig1:**
[figure not shown]
Overview of the Korean Laparoscopic Surgical Society (KLASS)-02 randomized controlled trial (RCT) design. RFS; relapse free survival, FU; follow up, PP; per protocol.

For analysis of relapse-free or overall survival, Kaplan-Meier curve analysis with log-rank tests will be used. To investigate the different proportions of patients with morbidity, mortality, or other categorical data between 2 groups, chi-square or Fisher’s extract tests will be applied. Continuous variables such as length of hospital will be evaluated using student t- or Mann–Whitney U tests. The level of significance will be set at 5%.

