### Study protocol

The Ajou ARO (Academic Research Organization) in Ajou University Hospital will manage this clinical trial. As soon as the participating surgeons obtain informed consent from the patients, researchers entered the patient information into an web-based electrical clinical report form (eCRF;http://clintrial.ajoumc.or.kr/klass02/). The beta version of eCRF system tested at each actual site before full implementation, to ensure data capture system and to reduce user error. The eCRF system is automatically given screening number according to the sequence in which the informed consent forms are received. And if patients meet the criteria for a randomization, then eCRF system assigned at each surgery group.. Finally, the system provides an allocation number with a pre-generated randomized code for those who are selected by inclusion and exclusion criteria. A randomized block design is applied for randomization with each investigator as the stratification factor (R 2.10.1). To maintain the properties of randomization, block size is not open to the investigators. The surgeons are immediately notified of the randomization results via e-mail. After notification, the surgeons let the patients know which type of operation they will undergo. Therefore, the surgeon and patient blinding is impossible owing to the nature of surgical RCT. However, the protocol recommends that ward staff members evaluating patient outcomes be blinded, if possible. If the surgeon does not perform the operation within 30 days after recruitment, the patients are excluded from the trial. These patients will need to be re-evaluated for re-recruitment into this RCT.

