### Outcome measurements

The primary endpoint of the KLASS-02 RCT is non-inferiority in the 3-year relapse-free survival rate after laparoscopic subtotal gastrectomy and extended lymphadenectomy for locally AGC compared with open conventional surgery. To measure this endpoint, the criteria for recurrence are suggested in detail. Recurrence can be detected on regular follow-up studies such as abdominopelvic CT in patients without specific symptoms through a formal radiology report. If the results of follow-up studies are suspicious, whole-body positron emission tomography-CT, magnetic resonance imaging of the liver, or laparoscopic exploration can be performed to confirm recurrence. Otherwise, patients can attend follow-ups at shorter intervals than the planned schedule. Patients with specific symptoms, such as abdominal mass, weight loss, or intestinal obstruction, which might coincide with recurrence, should be evaluated for recurrence immediately regardless of the follow-up schedule. Surgeon should report recurrence in enrolled patients by entering this information into the eCRF as soon as the recurrence is confirmed.

Secondary outcomes include postoperative morbidity and mortality, postoperative recovery, and quality of life. Complications are divided into early and late morbidities depending on time of occurrence. Early morbidity is defined as surgery-related complications occurring within 21 days postoperatively, and includes the events listed in Table 2. Complication severity is classified according to grading system suggested by Dindo D et al. [10]. Regarding postoperative morbidity, the operative time and blood loss volume are also recorded. In cases of conversion from laparoscopic to open surgery, the reason for conversion should be explained. The events related to late morbidity, which occur after the 28th postoperative day, are listed in Table 2.

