### Sample size calculation

The primary endpoint of this RCT is 3-year relapse-free survival of patients diagnosed with locally AGC. In an RCT conducted by Sakuramoto et al. [9], the 3-year relapse-free survival of gastric cancer patients who received TS-1 adjuvant chemotherapy and were diagnosed with stage II or III cancer on pathology from curative gastrectomy with D2 lymph node resection was 72% (hazard rate = 0.11). Therefore, the hazard rate of patients who underwent open conventional surgery in the control condition was 0.11 in the 3 year. In addition, the margin of non-inferiority assumed a hazard ratio (HR; hazard rate of group A/hazard rate of group B) of 1.43 according to the study design in the Sakuramoto et al., in which the HR of the surgery-only group was compared with that of the adjuvant group. The null hypothesis was assigned as HR ≥ HR_0_, and the alternative hypothesis as HR < HR_0_. Type I error was set at 0.25 (one-sided) with 90% power, and the sample size was calculated using the log-rank test for non-inferiority (PASS 12. NCSS, LLC. Kaysville, Utah, USA. www.ncss.com.).

As a result, a total of 1,050 patients (525 patients per group) with 330 target event as recurrence are required when we consider a 10% dropout rate.

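### The stated relapse-free survival analysis, log-rank tests at an unsided 5%, is not tied to the 1.43 hazard ratio margin, and its level is not reconciled with the design

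*Protocol article*

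**What the plan says.** Outcome measurements sets the aim: "The primary endpoint of the KLASS-02 RCT is non-inferiority in the 3-year relapse-free survival rate" of the laparoscopic arm against the open arm.

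Sample size calculation fixes the design. On the margin: "the margin of non-inferiority assumed a hazard ratio (HR; hazard rate of group A/hazard rate of group B) of 1.43". On the hypotheses: "The null hypothesis was assigned as HR ≥ HR_0_, and the alternative hypothesis as HR < HR_0". On the error rates: "Type I error was set at 0.25 (one-sided) with 90% power". On the method: "the sample size was calculated using the log-rank test for non-inferiority". The result is 330 events and 1,050 patients, allowing for 10% dropout.

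Patient groups for statistical analysis, in the paragraph after Figure 1, then gives the analysis: "For analysis of relapse-free or overall survival, Kaplan-Meier curve analysis with log-rank tests will be used". Categorical outcomes get chi-square or Fisher tests, introduced by "To investigate the different proportions of patients with morbidity, mortality, or other categorical data between 2 groups". One 5% significance level covers everything, without saying one-sided or two-sided.

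Safety assessment for early morbidity is also sized as non-inferiority: 20.9% complications, a 12% margin, one-sided 0.025, 90% power and 242 patients per group. The Discussion describes stopping if laparoscopy proves significantly worse on safety.

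**The concern.** Relapse-free survival, which has a margin, and overall survival, for which the article gives none, share one method in one sentence. A log-rank test with no shift asks whether the hazards are equal. Failing to reject equality is not evidence that the HR is below 1.43, and rejecting it in favour of laparoscopy would show superiority, which is not the aim. The text that says how the trial will be analysed therefore does not, on its face, answer the question for which the trial was sized.

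The level is also unsettled. The article prints 0.25 one-sided in one place and 5% without sidedness in another, and the event target implies a third value. The success criterion for the primary endpoint depends on which one is used.

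**Working it through.** **Inputs.** Margin 1.43, power 90% and 330 events (Sample size calculation); 5%, unsided (Patient groups for statistical analysis); 20.9%, 12 points and 242 per group (Safety assessment for early morbidity). Assumptions: 1:1 allocation (525 per group supports this), group A is the laparoscopic arm, and SE(ln HR) = 2/√events.

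**1. Reproduce the 330 events.** Schoenfeld: events = 4(z₁₋α + z₀.₉₀)² / (ln 1.43)², with ln 1.43 = 0.3577.

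| One-sided α | Calculation | Schoenfeld | Freedman |
|---|---|---|---|
| 0.025 | 4(1.960 + 1.282)² / 0.1279 | 329 | 336 |
| 0.05 | 4(1.645 + 1.282)² / 0.1279 | 268 | 274 |
| 0.25 (as printed) | 4(0.674 + 1.282)² / 0.1279 | 120 | 123 |

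Only one-sided 0.025 against HR 1.43 gives the stated figure. The trial was sized for a margin test at 0.025.

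**2. Decision thresholds at 330 events.** SE = 2/√330 = 0.1101.

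- Margin test, one-sided 0.025: the observed HR must be below 1.43 × exp(−1.960 × 0.1101) = 1.152. Power at HR = 1 is Φ(0.3577/0.1101 − 1.960) = Φ(1.289) = 90.1%.
- Margin test, one-sided 0.05: the observed HR must be below 1.43 × exp(−1.645 × 0.1101) = 1.193. The error at HR 1.43 is 5%, twice 2.5%.
- Equality log-rank, two-sided 5%: non-significant, or in favour of laparoscopy, for any observed HR below exp(1.960 × 0.1101) = 1.241.

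Observed HRs from 1.152 to 1.241 fail the margin test yet show no significant difference.

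**3. Error if non-significance counted as success.** At a true HR of 1.43 the probability is Φ(1.960 − 0.3577/0.1101) = Φ(−1.289) = 9.9%, against 2.5%. With 264 events (80% of target, chosen only for illustration) it is 17.2%. If a significant result in favour of laparoscopy were required instead, power at HR = 1 would be only 2.5%.

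**4. Safety comparison.** n = (1.960 + 1.282)² × 2 × 0.209 × 0.791 / 0.12² = 241.3, so 242 per group, as stated.

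- With 20.9% observed in the open arm, the upper 95% limit stays below 12 points only if the observed difference is below about 4.5 points: SE about 0.0383, and 4.5 + 1.96 × 3.83 = 12.0.
- The chi-square test is non-significant up to about 7.7 points: pooled SE about 0.0392, and 1.96 × 3.92 = 7.7.
- At a true excess of 12 points, chi-square is non-significant about 15% of the time; the margin test errs 2.5% of the time.

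**5. Strata.** Study protocol says "A randomized block design is applied for randomization with each investigator as the stratification factor". A simulation of the margin test assumed 13 or 20 surgeons, a between-surgeon SD of log hazard from 0 to 0.5, and about 300 to 390 events. The error at HR 1.43 was 2.3–3.3% unstratified and 2.1–2.8% stratified. Power was 91–94% and 91–93%. The effect is small.

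**The case against.** The strongest reply is that the analysis paragraph is shorthand. The sample size section states the margin, gives one-sided hypotheses and names a non-inferiority log-rank test, and the non-inferiority aim recurs throughout the article. A reader who puts the two sections together can build a correct analysis, and a two-sided 5% level applied to the margin is the same as one-sided 0.025. This stands as far as it goes. It rules out the stronger inference that the plan cannot deliver a non-inferiority conclusion. It does not remove the defect: the non-inferiority test is named only as the method of sizing, the analysis paragraph does not carry it over, and the 5% is not said to be two-sided.

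The 9.9% is conditional. The article never says that a non-significant result will count as success, and its hypotheses point the other way.

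On safety, the chi-square sentence is generic and does not mention the 484-patient analysis. A test of difference can also serve a rule that stops for significant inferiority. That makes the safety mismatch secondary, but the sizing and the stopping wording still follow different logic.

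A reader might also infer that the analysis ignores the surgeon strata. The article does not say so. It is silent, and a condensed article commonly leaves this to the full protocol or analysis plan.

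**Conclusion.** The point holds as a mismatch between the stated analysis and the stated hypothesis. Taken literally, the log-rank sentence tests HR = 1, while the design tests HR ≥ 1.43. The unsided 5% agrees with the one-sided 0.025 behind the 330 events only if it is taken as two-sided and applied to the margin, and the article says neither. It agrees with the printed 0.25 on no reading.

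At 330 events the size is a band of observed HRs, 1.152 to 1.241, in which the two tests point to different conclusions. The potential error is 9.9% (non-significance read as success) or 5% (one-sided 5% margin test), against 2.5%. These figures rest on 1:1 allocation, proportional hazards and the usual large-sample variance. The matter needs correcting because it governs the main conclusion, and the correction is confined to wording. The safety mismatch is real but secondary. Stratification is not part of the error.

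**What to change.** - State the primary relapse-free survival analysis as the HR (laparoscopic/open) with a two-sided 95% confidence interval, equivalent to one-sided 0.025. Non-inferiority is concluded if the upper limit is below 1.43. Kaplan-Meier curves and 3-year rates are descriptive.
- Reconcile the alpha values: the 0.25 in Sample size calculation and the 5% in Patient groups for statistical analysis, against the 0.025 that the 330 events imply. State sidedness wherever a level is given.
- State the 484-patient safety comparison as a risk difference with a 95% confidence interval, upper limit compared with the 12-point margin. The steering committee should reconcile this with the stopping wording in the Discussion, so that it is clear which result bears on continuation.
- Optional: stratify the Cox model by randomising investigator, pooling sparse strata by institution. The expected effect is small.

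The cost is analysis wording only. The number of patients, the number of events and the follow-up do not change.

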## Discussion

To the best of our knowledge, this study is the first multicenter randomized clinical trial recruiting a large number of patients to compare laparoscopic D2 lymphadenectomy with open conventional lymphadenectomy in patients preoperatively diagnosed with locally AGC. Through this clinical trial, we aim to show the non-inferiority in the 3-year relapse-free survival rate of patients undergoing laparoscopic procedures compared with open surgery as the primary end point. In addition, laparoscopic surgery is expected to show comparable surgical outcomes such as morbidity and mortality, and improved postoperative recovery. Particularly, we sought to design the trial to overcome the challenges confronting surgical clinical trials while following the general principles of multicenter RCTs.

In general, multicenter RCTs should be designed according to specific principles such as evidence-based calculation of sample size, concealment of randomization, interim analysis, ITT analysis, and blinding to the type of intervention to avoid bias. Our protocol was established by following these general principles as closely as possible. However, blinding of the surgeons and patients to the intervention is impossible in most surgical clinical trials. In particular, when comparing laparoscopic surgery with conventional laparotomy as in the present RCT, blinding between 2 surgical procedures cannot be achieved due to the technical difficulty. In some previous surgical RCTs, postoperative dressings were applied using the same methods for patients who underwent both laparoscopic and open cholecystectomy, thus the type of intervention was blinded to patients and ward staff [14,15]. However, it is unlikely that perfect blinding using the same dressing is achieved, and blinding patients to the type of surgery might cause ethical issues. Non-blinding of staff investigating the outcomes will likely cause subjective measurement of them. To minimize the bias due to non-blinded randomization in the present RCT, we suggested the objective outcomes as endpoints. Therefore, the criteria for recurrence, the primary endpoint of this RCT, were described in detail.

Our clinical trial was proposed at an opportune moment in the development of gastric cancer surgical approaches. To date, laparoscopic surgery has been described as a revolutionary procedure to minimize the trauma in various fields of surgery, including gastric cancer surgery. Laparoscopic limited lymphadenectomy (D1 or D1+) has been widely performed by experienced surgeons as a treatment for EGC, but not AGC [5,6]. The canonical procedure for locally AGC is gastric resection with extended lymphadenectomy (D2), as the long-term results of several RCTs have reported superiority in the survival rate of patients who underwent D2 lymphadenectomy relative to that of limited lymphadenectomy (D1) [16,17]. In contrast to limited lymphadenectomy, D2 lymphadenectomy requires dissection of the groups of lymph nodes around major vessels such as the hepatic (LN #8) and splenic (LN #11p) arteries and the portal vein (LN#12a). Owing to limitations of the laparoscopic view for these lesions, the principle of surgery for patients with locally AGC is D2 lymphadenectomy with open laparotomy. However, a recent case-matched study reported by the KLASS group showed that there was no difference in long-term survival rates between laparoscopic and open conventional gastrectomy in AGC patients [18]. Moreover, several non-randomized clinical studies have shown the oncologic feasibility and technical safety of laparoscopic D2 lymphadenectomy for AGC [19-21]. Particularly, experienced surgeons have claimed that the advanced laparoscopic instruments and imaging system enables them to dissect the groups of lymph nodes in extensive regions such LN#8, #11p, and #12a. Considering the conclusive benefit of laparoscopic surgery in postoperative recovery, expansion of laparoscopic surgery is inevitable as long as the clinical evidence is clarified. Therefore, this multicenter RCT investigating the efficacy of laparoscopic surgery in patients with locally AGC is warranted to confirm the utility of laparoscopic surgery in patients with gastric cancer.

Although a clinical trial of laparoscopic D2 lymphadenectomy seems feasible based on previous reports, we could not ignore the internal validity of the laparoscopic skill of the surgeons participating in this RCT. This issue could be problematic, as the procedures will be performed by numerous surgeons. Therefore, we established several rules to avoid problems related to internal validation. First, only surgeons who had performed ≥50 laparoscopic gastrectomies for gastric cancers and were affiliated with experienced institutions could participate in this RCT. This principle is based on previous reports in which laparoscopic surgery for gastric cancer required some experience to overcome the learning curve [22-24]. Second, we performed a separate clinical study to validate the surgeons who wish to participate in this RCT (registered at www.clinicaltrials.gov as NCT01283893) [8]. Experts review the videos submitted by candidate surgeons, and the committee decides whether they can participate in this study based on the reviewers’ results. Third, the participants will submit videos of their laparoscopic surgeries and photos of conventional open surgery every 10 recruitments for the committee’s review. These efforts to maintain internal validity will be helpful to ensure that meaningful results are obtained from this RCT.

The safety of laparoscopic D2 lymphadenectomy should be emphasized, because this study is the first multicenter RCT to evaluate its efficacy. In our RCT, morbidities related to surgeries will be investigated separately during early and late postoperative periods after surgery. Since most late complications such as reflux and intestinal obstruction are mainly related to reconstruction methods regardless of the type of laparoscopic or open laparotomy, we eventually focused on early postoperative morbidity to evaluate safety. When the number of patients recruited in this RCT reaches 484, the data related to early postoperative morbidities will be analyzed to determine whether laparoscopic surgery for D2 lymphadenectomy is less safe compared with open surgery. The number of patients required for this safety analysis was calculated according to previous RCTs, which reported that the complication rate of D2 lymphadenectomy was 20.9% in an RCT performed by Japanese surgeons, and the limitation of non-inferiority for complications of D2 lymphadenectomy compared with D1 was 12.0% in another Italian RCT [11,25]. This protocol includes a plan to stop recruitment and discontinue this RCT if the results of the safety analysis show significant inferiority in the safety of laparoscopic groups relative to the conventional group.

In conclusion, the KLASS-02 RCT was designed to show the efficacy of laparoscopic D2 lymphadenectomy in AGC patients compared with the open procedure. We attempted to highlight the principle of surgical clinical trials, and the internal validity of surgeons participating in this RCT was considered. Finally, we hope to suggest our RCT to other researchers who wish to conduct a well-designed, organized surgical clinical trial.

## Abbreviations

JGCA: Japanese Gastric Cancer Association
RCT: Randomized clinical trial
EGC: Early gastric cancer
AGC: Advanced gastric cancer
KLASS: Korean laparoscopic gastrointestinal surgery study group
ARO: Academic Research Organization
DSMC: Data and safety monitoring committee
ARO: Academic Research Organization
CT: Computed tomography
EORTC: European Organization for Research and Treatment of Cancer
IIT: Intension to treatment
FAS: Full analysis set
PP: Per protocol
